##### Semi-structured interviews

3.2.6.2

Semi-structured interviews will be conducted to assess participants’ perspectives and opinion regarding the multicomponent exercise intervention they received. The interviews will involve some broad open-ended questions about their experience and acceptability of the intervention. See Table 3 for the interview guide.

**Table 3 tab3:** Interview guide.

Interviewing questions for the perception of the multicomponent exercise intervention
1. How do you feel about the multicomponent exercise intervention? [probes: content, format, arrangement]
2. How would you describe your participation in this multicomponent exercise intervention?
3. Are there any barriers or hindering factors for your participation in this intervention? What are they?
4. Can you think of any strategies which can facilitate your participation in this intervention?
5. How does your health conditions change after engaging in this intervention? [probes: physical health, cognitive function, psychological health]
6. What are the possible reason for the changes in your health condition, if any? [probes: self-efficacy]
7. Does participating in this exercise training affect your daily life? Do your relatives and friends support your participation in this program?
8. Would you be willing to continue participating in this intervention program in the future? What are the reasons behind your decision?
9. Would you recommend this exercise program to your relatives and friends?
10. Is there anything else you would like to share with me about this exercise program?

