### Research hypotheses

3.1

To assess the impact of the multicomponent exercise intervention, our study hypothesizes several outcomes across physical, cognitive, mental, and quality-of-life domains. We aim to explore the potential effects of this intervention on various parameters and examine the mediating role of exercise self-efficacy.

(1) We hypothesized that participants who receive the multicomponent exercise intervention will report greater improvements in physical frailty, cognitive function, body composition, senior fitness, mental health, sleep quality, and health-related quality of life upon completion of the intervention compared to those in the control group.(2) We hypothesized that the effects of the multicomponent exercise intervention on physical frailty, cognitive function, body composition, senior fitness, mental health, sleep quality, and health-related quality of life are mediated through an increase in exercise self-efficacy.(3) No starting hypothesis has been established for the qualitative part of the study because it is oriented through an exploratory study.

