#### Sample size estimation

3.2.4

For the RCT, the sample size will be calculated using PASS software, based on improvement in the primary outcome (physical frailty) in this trial. Previous findings from a similar exercise program reported a reduction in physical frailty score of 0.22 in the control group and 1.59 in the intervention group (Sadjapong et al., 2020). Given a power of 90% and level *α* = 0.05, 34 participants are needed. Considering a 20% attrition rate, with 41 participants in each group, a total of 82 participants are needed. Regarding the qualitative interviews, a purposive subsample of 20 participants who have completed the multicomponent exercise intervention will be recruited.

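### The one interview question on why health changed has a single probe, the trial's own hypothesised mediator, and the question before it takes change for granted

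*Protocol article*

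**What the plan says.** Section 3.1 sets out three statements. The second is the mediation hypothesis: the effects on all health outcomes "are mediated through an increase in exercise self-efficacy". The third concerns the interviews: "No starting hypothesis has been established for the qualitative part of the study because it is oriented through an exploratory study". Section 3.2.6.1 then names exercise self-efficacy as the mediating factor, and section 3.2.10 tests it with mediation models.

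Section 3.2.6.2 describes the interviews in these terms: "The interviews will involve some broad open-ended questions about their experience and acceptability of the intervention". Table 3 prints the guide, which has ten questions. Two matter here:

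- Question 5: "How does your health conditions change after engaging in this intervention? [probes: physical health, cognitive function, psychological health".
- Question 6: "What are the possible reason for the changes in your health condition, if any? [probes: self-efficacy".

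Section 3.2.4 fixes the interview sample: "a purposive subsample of 20 participants who have completed the multicomponent exercise intervention will be recruited". Section 3.2.10 says that the transcripts will be coded by content analysis, by two authors working independently. The article gives no rule for marking whether a statement was volunteered or came after a probe.

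**The concern.** An interview strand that starts from no hypothesis should let participants name their own explanations. On the one question that asks for explanations, the interviewer is given one idea to suggest, and it is the idea that the trial hopes to confirm. A self-efficacy theme built on answers to that probe could not be told apart from a theme that the guide put there.

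Question 5 adds to this. By asking how health changed, it invites the interviewee to find a change, and question 6 then asks for its cause. Someone who noticed nothing has to contradict the question in order to say so.

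What is at stake is objective 3, the participants' own perception of the programme. A reader of the eventual report might also take a self-efficacy theme as separate support for the mediation hypothesis, when the interviewer may have introduced the topic.

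**Working it through.** No formula applies and the plan gives no figure to reproduce. The check is a reading of Table 3 against the stated hypotheses and the programme description.

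**Step 1: count the probes.**

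| Question | Topic | Probe terms | Number |
|---|---|---|---|
| 1 | Feelings about the programme | content, format, arrangement | 3 |
| 5 | Health change | physical health, cognitive function, psychological health | 3 |
| 6 | Reasons for health change | self-efficacy | 1 |
| 2, 3, 4, 7, 8, 9, 10 | Participation, barriers, facilitators, daily life and support, continuing, recommending, anything else | none | 0 |

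The total is 3 + 3 + 1 = 7 probe terms on 3 of 10 questions. Self-efficacy is 1 of 7 in the whole guide, but 1 of 1 on the only question about reasons for health change.

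**Step 2: compare that probe with the hypotheses.** The term is the mediator of hypothesis 2 (section 3.1) and the mediating factor of section 3.2.6.1. The same section 3.1 says that the qualitative part has no starting hypothesis.

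**Step 3: see whether the plan offers other reasons that could have been probed.** It does. The Background treats motivation and enjoyment as important for adherence and presents exergaming as an enjoyable form of exercise. Section 3.2.2 delivers the sessions in groups. Table 2 lists health education, social comparison, feedback, anticipated rewards and problem solving. None of these is a probe on question 6. The three-term probes on questions 1 and 5 show that the guide uses plural probes elsewhere.

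**Step 4: check the presumption of change.** Question 5 opens with "How does your health conditions change after engaging in this intervention". It names three domains and no direction, so a worsening can be reported, but it does not ask whether anything changed. Question 6 does carry the qualifier that there may have been no change, but only after question 5 has been put.

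**Step 5: check what the wording can reach.** The mediation models use the SEE scale (section 3.2.6.1.2), a scored questionnaire. The group comparisons use the measured outcomes. Neither takes input from the interviews.

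**The case against.** The best defence is that having no starting hypothesis means only that the interviews test none. A theory-informed probe is not a hypothesis, and a mixed-methods study may reasonably ask participants about the central construct of its framework. In a semi-structured interview a probe is optional and normally follows the free answer. Question 6 opens openly and allows for no change, and question 10 is fully open. Coding detail is also something that an article often leaves to the full protocol.

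Much of this stands. It rules out several stronger readings that a reader might infer:

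- *That the whole guide prompts only the mediator.* It does not. Six of the seven probe terms are something else, such as those in question 1: "How do you feel about the multicomponent exercise intervention? [probes: content, format, arrangement". The word only is true of question 6 alone.
- *That self-efficacy is bound to emerge as a theme.* The probe creates a risk of leading, not a certain result.
- *That the interviews are meant to corroborate the mediation models.* No sentence says so. Mechanism is objective 2 and is assigned to the models; the interviews are assigned to experience and acceptability.
- *That the interviews could prime the exercise arm before the week-12 questionnaires.* The article does not state the order of the interviews and the final assessment. The full protocol may fix it, and the study-design figure is not shown. Nothing here supports a claim of bias in the outcomes.

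The defence does not explain why the one question on causes offers a single cause when the programme description supplies many, or why question 5 does not ask whether health changed. Both are visible in the printed guide and depend on no unseen document.

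**Conclusion.** The point holds in a limited form and is minor. On the only question about reasons for health change, the sole probe is the trial's hypothesised mediator, and the preceding question presupposes change. This fits poorly with interviews described as exploratory and open-ended, and it weakens any self-efficacy theme that comes from prompted answers as evidence of the participants' own view.

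The size cannot be put as a number, because it depends on how often interviewers use the probe and how interviewees respond. The reach is clear: two questions in the guide meant for the 20 interviews, with no effect on the randomised comparisons, the primary outcomes or the mediation estimates. The conclusion assumes that the interviews follow Table 3 as printed and that the coding does not already separate prompted from volunteered statements. If a fuller document has such a coding rule, the suggestion to reword the two questions remains.

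**What to change.** Make three small changes before interviewing starts, since a prompted answer cannot be made unprompted afterwards:

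1. Reword question 5 so that it asks whether health became better, became worse or stayed the same, and keep the three domain probes.
2. In question 6, replace the single self-efficacy probe with a neutral one (for example, a request to say more about why), or with several drawn from the programme's own components, such as enjoyment, social contact, feedback, health education and self-efficacy. Alternatively, move self-efficacy to a closing question asked after all the open ones.
3. Add a coding rule that marks each mention of a reason as spontaneous or prompted, and report the two separately.

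The cost is two reworded questions, one coding rule and slightly more coding work. The small downside is that some interviewees may not raise self-efficacy unprompted. If the topic must be covered with everyone, the closing question secures it while keeping the open answers clean.

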#### Safety protocol

3.2.7

Several measures will be implemented to ensure participants’ safety during the intervention. (1) Participants meeting exercise contraindications or assessed as high risk for exercise-related injuries will be excluded. (2) Instructions for the exercise intervention will include healthy advice to prevent injuries. (3) Prior to each exercise session, the exercise supervisor will conduct a brief medical safety check following ACSM recommendations. (4) If the participant reports concerning health changes, alterations in medications/dosage, or exhibits abnormal vital signs (e.g., blood pressure ≥ 180/100 mmHg), their participation in activities will be immediately paused, until they are seen and cleared to proceed by the study physician. (5) Participants will periodically report their perceived effort level on the Borg Rating of Perceived Exertion scale during each session to ensure proper exercise intensity. (6) There will be a warm-up routine before each session, and a cool-down routine after completion. (7) A multidisciplinary team (e.g., nurses, geriatricians, physiotherapists) has been involved in designing and implementing this trial to eliminate possible risks and prioritize participants safety.

#### Ethics and dissemination

3.2.8

This study was approved by the ethics committee of Central South University (reference number E202249) and will be conducted according to the ethical standards of the Helsinki Declaration. After thoroughly discussing potential risks and benefits, written informed consent will be obtained from all participants before inclusion.

The study protocol has been registered and can be obtained through the Chinese Registry website (registered on ChiCTR.org with the identifier ChiCTR2200058850). The findings of the study will be published in scientific journals to target a wide range of groups and be reported at international conferences in the field of gerontology. Additionally, the results will be disseminated among study participants, healthcare professionals, healthcare providers and the public through courses, presentations, and online platforms.

#### Data management and security

3.2.9

All potential participants will be assigned a unique ID number at the start of the assessment to maintain the participants’ confidentiality. Any handwritten information such as written consent forms or other related research materials will be stored securely in a locked cabinet when not in use. All electronic data will be securely stored on a server within the principal investigator’s institute. All data will be analyzed anonymously.

#### Data analysis

3.2.10

Summary statistics, including means with standard deviations, frequencies, and percentages, will be generated for baseline characteristics. To compare the baseline characteristics between the two groups, Student’s *t*-test or the Wilcoxon rank-sum test will be utilized for continuous variables, while Chi-square or Fisher’s exact tests will be employed for categorical variables. Analysis of covariance (ANCOVA) and generalized linear models (GLM) will be performed to compare mean changes in continuous variables between the two groups. Adherence, dropout rates, program satisfaction, and adverse events will be tabulated and summarized using descriptive statistics. Mediation models will be used to test whether exercise self-efficacy mediates the relationship between the multicomponent exercise intervention and physical frailty, cognitive function, body composition, senior fitness, mental health, sleep quality, and health-related quality of life. Any missing data on outcomes will be approximated through multiple imputation. All analyses will be performed with the intention-to treat (ITT) principle. Two-sided tests will be performed for all analyses, and *p*-value less than 0.05 will be considered to be statistical significance. Additionally, sensitivity analyses will be adopted to assess the robustness of the findings based on the per-protocol analysis set.

Regarding qualitative data, audio-recorded interview will be transcribed word-for-word. Content analysis will be adopted to code the data on their perceptions of the intervention. Two authors will independently code the data, and any discrepancies will be resolved through discussion.

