###### Other collected data

3.2.6.1.5

Adherence to the program will be documented via an activity diary completed by the research assistants, and reasons for dropouts and poor adherence will also be documented. Reasons for dropout, including adverse events, medical problems, death, and participant decisions, will be collected. Program satisfaction will be evaluated using a self-designed questionnaire. Participants will rate their satisfaction based on perceived enjoyment of the training, the appropriateness of the content, the form of the training, the benefits obtained by the training, and the likelihood of recommending the program to others. Rating will use a 4-point Likert scale, with “1” indicating “not at all” and “4” representing “definitely.” Any adverse event, such as muscular soreness, falls, or injury, will also be recorded by the research team.

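### The only sensitivity analysis named is per-protocol, which cannot show whether the imputed intention-to-treat result survives informative dropout

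*Protocol article*

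**What the plan says.** Section 3.2.10 (Data analysis) makes three linked statements. On the analysis population: "All analyses will be performed with the intention-to treat (ITT) principle". On missing values: "Any missing data on outcomes will be approximated through multiple imputation". On robustness: "sensitivity analyses will be adopted to assess the robustness of the findings based on the per-protocol analysis set". The article names no other sensitivity analysis. It does not state the missing-data mechanism or the imputation model, and it does not define the per-protocol set.

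The main comparison is a between-arm contrast of change: "Analysis of covariance (ANCOVA) and generalized linear models (GLM) will be performed to compare mean changes in continuous variables between the two groups".

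Other sections set the context:
- Sections 3.2.1 and 3.2.6.1 place outcome measurement at two times only, baseline and the end of the 12 weeks.
- Section 3.2.4 allows for loss: "Considering a 20% attrition rate". It does not split this by arm.
- Section 3.2.6.1.5 expects some loss to be health-related: "Reasons for dropout, including adverse events, medical problems, death, and participant decisions, will be collected". It also has adherence recorded by the research assistants.
- Section 2 (Background) says adherence is often low in older people and largely decides whether exercise works. Section 5 (Limitations) accepts a risk of missing data and dropout.

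**The concern.** A sensitivity analysis is informative when it varies an assumption that the main result depends on and the data cannot verify. For an imputed intention-to-treat analysis, that assumption concerns how participants without a week-12 value would have scored. The per-protocol set does not vary it. To the extent that it leaves those participants out, it makes the same assumption in another way, namely that the people who remain can stand in for those who left.

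The design makes this matter. With no interim outcome visit, a participant lost before week 12 contributes only baseline outcome values. The control group receives no intervention, so someone who leaves the exercise programme early may end closer to a control than to a completer. If so, ordinary imputation and per-protocol would both overstate the effect of assignment, and by similar amounts. Their agreement would then be reported as robustness when it carries no information on the point.

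**Working it through.** **Inputs.** Section 3.2.4 gives reductions in frailty score of 0.22 (control) and 1.59 (intervention), 90% power, α = 0.05, 20% attrition and 41 per group. The split of dropout by arm and the outcomes of dropouts are not given. They are assumed below and varied.

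**The plan's own figures.** The planned difference is δ = 1.59 − 0.22 = 1.37. The step to 41 follows from 34 × 1.2 = 40.8 (34 / 0.8 would give 43). The 34 itself ("0.05, 34 participants are needed") cannot be reproduced, because no standard deviation is stated. Read as 34 per arm, two-sided, it implies SD = 1.37 / (3.2415 × √(2/34)) = 1.74. Read as a total of 34, it implies 1.23. The percentages below use neither value.

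**Size of the overstatement.** Let q be the share of the exercise arm lost before week 12 and k the fraction of the benefit they keep. Take control dropout as uninformative. The effect of assignment in everyone randomised is

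δ × [1 − q(1 − k)].

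Imputation within arm under missing at random estimates δ, as does an analysis of completers. The relative excess is 1 / [1 − q(1 − k)] − 1, which depends on neither the SD nor δ.

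| q | k | Effect of assignment | Imputed or completers | Excess |
|---|---|---|---|---|
| 10% | 0 | 1.23 | 1.37 | 11% |
| 10% | 0.5 | 1.30 | 1.37 | 5% |
| 20% | 0 | 1.37 × 0.8 = 1.10 | 1.37 | 25% |
| 20% | 0.5 | 1.23 | 1.37 | 11% |
| 30% | 0 | 0.96 | 1.37 | 43% |
| 30% | 0.5 | 1.16 | 1.37 | 18% |

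If k = 1 (dropouts resemble completers) there is no excess.

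**Offset from the control arm.** If a share r of controls drop out and end c points worse than control completers, the net bias is q(1 − k)δ − r × c. At q = r = 20% and k = 0, the first term is 0.2 × 1.37 = 0.274. Full cancellation needs c = 0.274 / 0.2 = 1.37.

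**Do the two analyses move together?** This was simulated with 1,000 trials, 41 per arm, 8 missing per arm and an assumed SD of 1.74. Imputation was by regression within arm, with 20 imputations pooled by Rubin's rules. The per-protocol set was taken as completers.
- Exercise dropouts end like controls: mean effect with full data 1.09, multiple imputation 1.36, per-protocol 1.36. The two methods gave the same significance verdict in 97.7% of trials. A delta-adjusted imputation with a shift of 1.37 in exercise dropouts returned 1.10.
- The same scenario with treatment arm left out of the imputation model: multiple imputation gave 1.09.
- No true effect, with exercise-arm dropout tied to poor change (assumed correlation about 0.6): multiple imputation and per-protocol both averaged 0.34, and both were significant together in 10.6% of trials.

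The near-identity is expected. When only the week-12 outcome is missing and the imputation uses little beyond arm and baseline, multiple imputation adds almost nothing to an analysis of completers.

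**The case against.** The strongest reply is that this is detail for a statistical analysis plan. Imputation models and missing-data sensitivity analyses are often left out of an article, and a per-protocol check beside an ITT analysis is conventional. It also answers a fair question about adherence, which the Background treats as central. That would dispose of a complaint that a tipping-point analysis is merely absent. It does not dispose of this one, because the article itself gives the robustness role to an analysis that cannot fill it. A fuller plan may name others, so the claim is limited to what the article names.

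Four stronger readings are tempting, and the documents do not support them.
- A reader might infer that the plan specifies missing-at-random imputation. It does not. That, and treatment arm in the model, are the usual defaults. If arm were omitted, the imputation would not share the optimism, although per-protocol would still not test the assumption about dropouts.
- A reader might infer that nothing is known about dropouts after baseline. Outcomes are not, but adherence, reasons for dropout and adverse events are recorded and could inform the imputation.
- A reader might infer that the per-protocol set removes exactly the dropouts. It is undefined, and may also exclude poor adherers who were assessed at week 12 and count fully under ITT. The two results could then differ, but the difference would mix adherence with missingness.
- A reader might convert the smaller effect into a loss of power. The article gives no SD, so no such figure is claimed.

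It also stands that the simulation scenarios are chosen, with informative loss in the exercise arm only, and that the article has no data on how dropouts fare.

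**Conclusion.** The point holds in a conditional form and should be corrected. As written, the only named check on robustness cannot detect informative dropout, and under the usual imputation model it would tend to agree with the primary result whether or not that result is biased.

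The 25% figure is an illustration. It assumes 20% loss in the exercise arm, dropouts who end like controls, uninformative loss among controls, and imputation under missing at random with arm in the model. The 5% to 43% range keeps the last two assumptions and varies the first two. The documents do not establish that the trial's estimate will be biased, or in which direction. The listed dropout reasons and the stress on adherence make a bias towards exercise plausible, and the plan as stated could not reveal it.

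**What to change.** Keep multiple imputation as the primary approach and amend section 3.2.10 in two sentences:
1. For both primary outcomes (frailty score and MoCA), name as the missing-data sensitivity analysis, on the ITT set, either a delta-adjusted imputation with a tipping point or a control-based imputation for exercise-arm dropouts. For frailty, the shift could run from 0 to the planned difference of 1.37. For MoCA the article gives no planned difference, so the tipping point should be reported and judged for plausibility. Applying shifts to control dropouts as well would cover the possible offset.
2. Describe the per-protocol analysis as supplementary, addressing adherence and not robustness to missing data.

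Stating the assumed mechanism, whether arm is in the imputation model, and whether recorded adherence and dropout reasons enter it would remove the inference made here. Sample size, visits and conduct do not change. The cost is a little more programming and a sensitivity estimate that may be less favourable than the primary one.
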